### Blinding Procedures

This will be a double blind design, in which trial participants, researchers providing the interventions and outcome assessors will be blinded to the intervention. This will be achieved using study mode of the devices and employing sham procedures for the α-tACS. Participants will be unblinded if they experience any unexpected adverse effects. At the end of their participation, blinding assessment will be performed to both participants and researchers who assessed the outcomes, namely by asking about the stimulation that they thought they had received (or applied) and to rate how confident they are in their guesses.

### Assessments

#### Useful Field of View (UFOV)

UFOV is a very well validated instrument to assess speed of processing and will be administered before the intervention and at the end of week 3 (see Figures 1, 2). This time point was chosen in order to minimize loss to follow-up. As there is some evidence that there may be a ceiling effect of CT (which may be the case for SoP also), we will also collect a co-primary endpoint at the end of the training (i.e., week 6; see Figures 1, 2).

#### NIH EXAMINER

The NIH Executive Abilities: Measures and Instruments for Neurobehavioral Evaluation and Research-EXAMINER battery will be used to assess transfer effects to untrained domains, such as executive function, insight or social cognition and behavior (Kramer et al., 2014). The NIH EXAMINER was previously developed to be used as a trial endpoint, and is organized into subtests targeting working memory, inhibition, set shifting fluency, insight, planning, social cognition and behavior, that allows us to obtain an executive composite score for each individual.

#### EEG Data

EEG data will be acquired using a 8-channel Loop-IT (Neurocare, Ilmenau, Germany) following the 10/20 system, in a continuous mode at a digitization rate of 500 Hz, with a bandpass filter of 0.01–100 Hz. The EOG will be recorded from two additional bipolar channels. Electrode impedances will be kept below 5 kΩ. We will be especially interested in changes in α- power, P300 from the oddball task, Event Related Desynchronization (ERD; for alpha attenuation) and Phase amplitude coupling (PAC; mainly α−γ).

#### MOCA, MMSE, and GDS

Participants will be screened using the Montreal Cognitive Assessment (MOCA; Nasreddine et al., 2005) and the Mini-mental State Examination (MMSE; Folstein et al., 1975). The Geriatric Depression Scale (GDS) short version (Yesavage and Sheikh, 1986) to track depression levels that could be used as a covariate in the analysis.

### Data Management and Access to Data

Collected data will be handled and stored accordingly to national and international regulations, always respecting the best (and stringent) practices available. All personal data will be de-identified and coded. The code will be stored in a locked storage with restricted access. Digital data will be stored using REDCap. A secure encrypted OneDrive will be used for the EEG data. We will use EEGLab, Matlab and SPSS version 28 to perform the data analysis. All further processing of data will follow an ethics committee approval and the data used will remain de-identified and coded, following the data-sharing agreement.

### Statistical Analysis

#### Primary Outcome

We expect that all groups, after the intervention, have increased performance in the UFOV scores, however we also expect that the group with the combined active α-tACS and SoP training would present the largest increase in scores, when comparing to either intervention alone. This will be tested by calculating the delta (week 3 or 6—baseline), and by performing independent one-way ANOVAS with intervention as a factor. Moreover, with the present design, we can track the intervention effects in several time points, namely between baseline, at week 3 and 6 of the interventions. This will be performed by means of an exploratory mixed model-ANOVAS, with time as within subject factor and intervention as between subject factor. As we cannot control at this point for several variables such as gender, depression or years of education, if there are significant differences between groups after randomization, we will include those covariates in the analysis, performing ANCOVAS instead of ANOVAS.

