## Abstract

Several cognitive training programs, alone or in combination with non-invasive brain stimulation have been tested in order to ameliorate age-related cognitive impairments, such as the ones found in Mild Cognitive Impairment (MCI). However, the effects of Cognitive Training (CT)—combined or not—with several forms of non-invasive brain stimulation have been modest at most. We aim to assess if Speed of Processing (SoP) training combined with alpha transcranial alternating current stimulation (α-tACS) is able to increase speed of processing as assessed by the Useful Field of View (UFOV), when comparing to SoP training or active α-tACS alone. Moreover, we want to assess if those changes in speed of processing transfer to other cognitive domains, such as memory, language and executive functioning by using the NIH EXAMINER. We also want to test the mechanisms underlying these interventions, namely brain connectivity and coherence as assessed by electroencephalography (EEG). To that purpose, our proposal is to enroll 327 elders diagnosed with MCI in a double-blinded, parallel randomized clinical trial assessing the effects of combining SoP with alpha endogenous tACS (either active or sham) in people with MCI. Participants will perform an intervention that will last for 15 sessions. For the first 3 weeks, participants will receive nine sessions of the intervention, and then will receive two sessions per week (i.e., booster) for the following 3 weeks. They will then be assessed at 1, 3, and 6 months after the intervention has ended. This will allow us to detect the immediate, and long-term effects of the interventions, as well as to probe the mechanisms underlying its effects.

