### Trial Design, Setting, and Registration

The trial will be an exploratory three arm parallel group, double blinded controlled trial, with an 1:1 allocation (see Figure 1). Data will be collected from clinical outpatient services from the Northern and Center Regions of Portugal. This trial has been registered at Clinicaltrials.gov with the identifier: NCT05198726.

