### Sample Size

No previous studies using tACS and SoP have used UFOV as a primary outcome, and as such, we are using the UFOV test-retest data from Bentley et al. (2012). For older adults the mean (SD) test-retest difference (i.e., consistency between measurements at two different timepoints on the same sample) between UFOV applications was 56.2 (74.8). In order to show an effect, our intervention should at least surpass the mean test-retest difference. So we ran three different scenarios: 0.50, 0.75, and 1.00 SD below mean difference for older adults, with a power of 0.8 and alpha of 0.05. In these scenarios, a minimum of 17 participants and a maximum of 64 per group would be required in order to detect a Cohen’s d of 1 and 0.5, respectively. However, these values were above the mean test-retest difference for younger adults, namely 31.5 (43.7). As such we used this value as our cut off point, and with a power of 0.8 and alpha of 0.05 we would need at least 98 participants per group. If an attrition rate of 10% is considered, 109 participants per group will be required. However, having trial feasibility into consideration, we decided to conduct a interim analysis for futility as soon as 19 participants per group are reached, then at 32 participants per group and finally at 71 participants per group (always considering the 10% attrition rate).

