## Discussion

The current work describes a protocol for a parallel, randomized, double-blind sham controlled trial to test the effects of the combination of active α-tACS with Speed of Processing (SoP) training, in trained (as measured by the UFOV) and untrained domains (as measured by the NIH EXAMINER), in people with Mild Cognitive impairment (MCI). Assessing trained transfer effects to other cognitive domains (and even to daily life activities) are extremely important, as the current literature is full of mixed results concerning the transfer effects of cognitive training (Sala and Gobet, 2017).

With the present design we expect that all groups will improve, however we expect that the combined intervention will be better at target engagement, and as such, participants on that specific arm, will improve more than the others. So what we aim to address with the current protocol is if the combination of SoP and active α-tACS is better than any intervention alone. It is important to note, that the current design is not a full factorial (i.e., there is no placebo intervention alone). This was a choice, as an inclusion of another group would increase the costs of trial, jeopardizing its feasibility.

Moreover, the current protocol also aims at studying the underlying mechanisms of the intervention. By studying the mechanisms underlying the interventions, it is possible to understand the role of the underlying neural circuitry (Gonçalves et al., 2016) as well as to detect specific candidates for brain biomarkers, which could be used to guide interventions, or to serve as outcome predictor (Yavari et al., 2016; Ovadia-Caro et al., 2019).

For instance, by using electrophysiological measures, during baseline and post-intervention, it will be possible to probe for connectivity changes within the brain, especially in the resting state networks. Moreover, it will be possible to unravel how those changes in connectivity relate to cognitive performance within the “disconnected brain” framework (Fjell et al., 2013, 2016). Furthermore, it will be possible to study potential phase amplitude coupling (PAC) between the alpha and other EEG bands, such as the gamma (γ; Canolty and Knight, 2010), which is thought to be responsible for memory and attentional processes (Herrmann and Mecklinger, 2001). By understanding such changes in the brain, the required algorithms for EEG guided stimulation closed-loops can be further developed (Leite et al., 2017).

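### The primary test is an omnibus three-arm ANOVA, which can be significant when the combination adds nothing to SoP training alone

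*Protocol article*

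**What the plan says.** The design is an "exploratory three arm parallel group, double blinded controlled trial, with an 1:1 allocation" (Trial Design, Setting, and Registration). The arms are the combination, SoP training with sham tACS, and active α-tACS with sham SoP. The Discussion says that there is no placebo-only arm, so the sham SoP task can only belong to the α-tACS-alone arm.

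The question is put the same way in three places:
- Abstract: the combination is assessed on UFOV "when comparing to SoP training or active α-tACS alone".
- Statistical Analysis, Primary Outcome: the combined group "would present the largest increase in scores, when comparing to either intervention alone".
- Discussion: the aim "is if the combination of SoP and active α-tACS is better than any intervention alone".

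The Primary Outcome analysis then ties the hypothesis to a test: "This will be tested by calculating the delta (week 3 or 6—baseline") and "by performing independent one-way ANOVAS with intervention as a factor". There is one ANOVA per time point. Week 3 is the primary endpoint and week 6 is called co-primary.

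The other UFOV analyses (the exploratory mixed-model ANOVA, the ANCOVA used on imbalance, and the chi-square tests on reliable change) also enter intervention only as an undirected factor.

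On size, the Sample Size section states, for power 0.8 and alpha 0.05, that "we would need at least 98 participants per group".

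**The concern.** Beating each intervention alone is a statement about two differences, both of which must favour the combination. A one-way ANOVA on three arms tests whether all three means are equal. Rejecting that says that some arm differs from some other. It does not say which arm, or in which direction.

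One failure case is plausible here. The Discussion calls UFOV the trained domain, and the α-tACS-alone arm does a task at a fixed exposure time in place of adaptive training. Both SoP arms could therefore do better than that arm even if stimulation contributes nothing. The named primary test could then be significant while leaving open whether α-tACS adds anything to SoP training, which is the reason for running the trial.

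**Working it through.** **1. Reproducing the planned sample size.** Inputs are from the Sample Size section: test-retest difference 56.2 (SD 74.8) in older adults and 31.5 (SD 43.7) in younger adults, power 0.80, alpha 0.05. Sidedness is not stated; two-sided is assumed.
- Difference: 56.2 − 31.5 = 24.7
- Pooled SD: √((74.8² + 43.7²)/2) = 61.26
- d = 24.7/61.26 = 0.403
- Two-group t-test: n = 97.5, so 98 per group. With 10% attrition, 98/0.9 = 108.9, so 109, and 3 × 109 = 327.

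The figures 98, 109 and 327 all reproduce, but as a two-group comparison. Using an SD of 74.8 alone gives 145 per group, and 43.7 alone gives 51. The value 0.403 is reconstructed and is not printed in the article.

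**2. The F test when the combination equals SoP alone.** Take standardised gains (d, d, 0) for combination, SoP alone and α-tACS alone, with n = 98 per arm. The noncentrality is λ = n·Σ(mean − grand mean)² = 98 × (2/3)d². Power is P(F > 3.03) for a noncentral F with 2 and 3 × 97 = 291 df. The article gives no SoP-versus-α-tACS gap, so d is varied.

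| Assumed gap d (SD) | λ | P(F significant) |
|---|---|---|
| 0.2 | 2.61 | 0.28 |
| 0.3 | 5.88 | 0.57 |
| 0.4 | 10.45 | 0.83 |
| 0.5 | 16.33 | 0.96 |

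In every row the combination adds exactly nothing to SoP.

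**3. The F test when the combination truly beats both.** With gains (d, 0, 0), λ is again 98 × (2/3)d². At d = 0.403 both patterns give λ = 10.62 and a rejection probability of 0.835. A significant F therefore cannot tell the two situations apart.

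**4. Alternative decision rules** (simulation, 98 per arm, pooled three-arm variance, d = 0.403).

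| Rule | Success when combination = SoP > α-tACS | Success when combination beats both |
|---|---|---|
| F significant | 0.835 | 0.835 |
| F significant and combination mean largest | 0.42 | 0.83 |
| Both contrasts significant, two-sided 0.05 | 0.025 | 0.69 |
| F significant, then both contrasts | 0.025 | 0.69 |

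The first column is false success. A single contrast has power 0.80, as planned.

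**5. Size needed for 0.80 on both contrasts.** About 121 evaluable per arm gives 0.80. With 10% attrition, 121/0.9 = 134.4, so 135 per arm and 3 × 135 = 405 in total, against 327 planned.

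**The case against.** The strongest reply is that this is a condensed article and that follow-up comparisons after a three-group ANOVA usually sit in an analysis plan, which is not shown. That stands as far as the absence of post-hoc detail goes, and the point does not rest on it. It rests on what the article does say: it names the ANOVA as the test of a hypothesis that the ANOVA does not address.

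It is also fair that the article nowhere says a significant F alone will be reported as superiority. The rejection rates above describe what that test can show, not what the authors will claim.

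Three stronger readings are tempting and are not supported:
- A reader might infer that a significant ANOVA would most likely reflect SoP training against none. The documents give no SoP-versus-α-tACS difference on UFOV, all groups are expected to improve, and the sham task still presents objects. At an assumed gap of 0.2 SD the F rejects only 28% of the time.
- A reader might infer that the plan promised 0.80 power for winning both comparisons. It attaches 0.8 to a per-group size and makes no statement about a joint win.
- A reader might infer that the ANOVA has to go. Keeping it as a gate before the two contrasts changes almost nothing, as the last row of the second table shows.

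The exploratory label lowers the stakes. But the plan also fixes a primary and a co-primary endpoint, an alpha and a power, so the primary test should still match the question.

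**Conclusion.** The point holds: the primary test as named does not test the stated claim. The size of the problem depends on how far α-tACS alone falls short of SoP training. The F test is significant, with no added benefit of the combination, in about 28% of trials at a 0.2 SD gap and 96% at 0.5 SD. Requiring both contrasts brings false success down to about 2.5%.

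The planned 0.80 applies to one pairwise comparison at d ≈ 0.403. If the combination is better than both single interventions by that amount, power to win both is about 0.69. The sample size arithmetic itself is not at fault.

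These figures assume normal data, equal SDs across arms, 98 evaluable per arm, two-sided 0.05 and the reconstructed d.

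**What to change.** - State that the claim rests on two pre-specified contrasts of the week 3 change in UFOV, taken from the same model: combination minus (SoP + sham tACS), and combination minus (active α-tACS + sham SoP).
- Claim superiority only if both favour the combination at two-sided 0.05. Because both are required, no alpha split is needed within one time point. Keep the ANOVA as a gate or as a descriptive result.
- State how the co-primary week 6 enters, for example tested by the same two contrasts only after week 3 succeeds. If success at either week could carry the claim, multiplicity across the two time points remains.
- State in the Sample Size section that 0.80 refers to one two-group comparison at d about 0.403, and that power to win both contrasts at that effect is about 0.69.

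The cost is a few sentences and a less favourable power figure. No new arm, visit or measurement is needed at the planned size. Restoring 0.80 for both contrasts would be a separate decision, at about 405 enrolled in place of 327.

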## Methods

### Purpose, Primary, and Secondary Outcomes

#### Primary Outcomes

The primary outcome will be changes from baseline in the *Useful Field of View* (*UFOV*) Assessment at week 3. UFOV is a good indicator of visual processing speed (Ball et al., 1988). The endpoint at week 3 was chosen because it is at the end of the intensive phase, and will be complemented by a co-primary endpoint at week 6 (after booster sessions). Long-term effects will be assessed at 1, 3, and 6 months after the stimulation has ended.

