Another important aspect of this study protocol is the understanding of the long-term effects of the intervention. The first follow-up assessment will occur at 1 month after the intervention has ended, and will be repeated at 3 and 6 months (see Figure 2). These long-term assessments are extremely important, as there is substantial evidence for placebo effects in healthy volunteers due to CT. In a recent study, participants that responded to a catchy flyer, suggesting that they were going to undertake a 1 h CT that would improve their cognitive performance and their fluid intelligence, improved between 5 and 10 points in a standard IQ scale; while those that responded to a nonsuggestive flyer (i.e., participating in a 1 h session in exchange for course credits) did not (Foroughi et al., 2016). This study highlights the importance of accounting for placebo effects when assessing the effects of CT. Despite the fact that there is no clear framework for estimating the duration of placebo effects, there are suggestions that the placebo effects may last up to 6 or 12 months (Hansen et al., 1996; Previtali et al., 2021). We will be using reliable change index (RCI) in order to assess if the changes in participant’s performance across time are reliable or not (Barker-Collo and Purdy, 2013). By using multiple assessments and especially the RCI we expect to mitigate any possible confounders arising from placebo effects.

The main challenge will be the loss to follow-up. Nonetheless, the team will focus on developing strategies to minimize this, such as sending reminders (phone, letter or email), by involving caregivers in the process, among others. If participants are not able (or willing to perform the EEG during follow-up), they will be offered the opportunity to perform the remaining follow-up assessments remotely, using videoconference systems, by phone or by the means of server based cognitive tasks.

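### The separate change-score ANOVAs drop anyone lost after week 3 from the week-6 co-primary analysis; a baseline-adjusted repeated-measures model would keep them and also gain precision at week 3

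*Protocol article*

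**What the plan says.** The article's Primary Outcomes section names UFOV change from baseline at week 3 as primary and says it "will be complemented by a co-primary endpoint at week 6 (after booster sessions"). The Assessments section explains week 3: "This time point was chosen in order to minimize loss to follow-up".

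Under Statistical Analysis, Primary Outcome, both endpoints are tested by taking the difference between week 3 or week 6 and baseline, and then "by performing independent one-way ANOVAS with intervention as a factor". The course over baseline, week 3 and week 6 is examined by "exploratory mixed model-ANOVAS, with time as within subject factor and intervention as between subject factor". Covariates enter only if the groups differ significantly after randomisation. The examples given are gender, depression and years of education; baseline UFOV is not among them.

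Sample Size moves from 98 to 109 per group for 10% attrition and does not say when that attrition occurs. The Outcomes section treats analysis as exploratory once dropout reaches 20%. That sentence closes the paragraph on EEG, so its reach to UFOV is not clear.

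**The concern.** The point concerns the estimator that the article names, not silence about missing data. A change score cannot be formed without the later visit. A participant measured at baseline and week 3 but not at week 6 is therefore absent from the week-6 ANOVA. The same participant is absent from the mixed ANOVA if that is run in its classical form, which needs every visit.

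The discarded week-3 value is the best available predictor of the missing week-6 value. If poor responders at week 3 leave more readily in one arm than in another, the week-6 completers in that arm are a favourable selection and the comparison tilts towards it. Enrolling 109 instead of 98 per group protects power but does nothing about this selection.

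**Working it through.** **1. The plan's own figure.** Inputs from Sample Size: older adults' test-retest difference 56.2 (SD 74.8), younger adults' 31.5 (SD 43.7), alpha 0.05, power 0.80.

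- Implied target: 56.2 − 31.5 = 24.7. The article does not state this number; it is inferred because it reproduces the result.
- Averaged SD: √((74.8² + 43.7²)/2) = 61.26.
- Standardised effect: 24.7/61.26 = 0.403.
- Two-sided two-sample t test: 97.5, so 98 per group. 98/0.9 = 108.9, so 109; 3 × 109 = 327. All agree with the article.
- SD 74.8 alone would give about 144 per group, so 61.26 is the SD that belongs with the 24.7 target.

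**2. Power lost to dropout.** With 98 per group analysed, power is 80%. With all 109 it would be 84%. At 10% attrition, therefore, no handling of missing data can recover more than about 4 points. In simulation a repeated-measures likelihood model without baseline adjustment recovered 0 to 1 point at week 3 and about 1 point at week 6 (random dropout). At 20% dropout it recovered at most 2 points. Power is not the main issue.

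**3. Bias at week 6, moderate scenario.** Assumptions, none from the documents:

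- two arms of 109, with 1500 runs per setting;
- equal correlation between visits of 0.5, 0.7 or 0.8, which makes the correlation between week-3 and week-6 change 0.5 in every case;
- half the dropout at random before week 3 and half after it;
- after week 3, random loss in one arm, and in the other a loss probability proportional to exp(z), where z is the standardised shortfall in week-3 change.

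Under this mechanism leavers average 1 SD worse at week 3. With a fraction p lost after week 3, those who stay are shifted by p/(1 − p) SD, and the week-6 contrast by p/(1 − p) × 0.5 × 61.26:

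| Total dropout | p after week 3 | Formula | Simulated bias, change score | Share of 24.7 | Mixed model |
|---|---|---|---|---|---|
| 10% | 0.05 | 0.0526 × 0.5 × 61.26 = 1.6 | 1.4 to 1.7 | 6–7% | about 0 |
| 20% | 0.10 | 0.1111 × 0.5 × 61.26 = 3.4 | 3.2 to 3.5 | 13–14% | about 0 (at most 0.3) |

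The simulation error of each mean is about 0.2 points, so the residual 0.3 is compatible with zero.

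**4. If dropout depends on the unseen week-6 value (not at random).** The change-score bias is 3.2 to 3.5 points at 10% dropout and 6.4 to 6.5 at 20%. The mixed model is still off by 2.3 to 2.5 and 4.3 to 4.7, so it removes only about a quarter to a third.

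**5. Extreme bound.** Suppose all dropout falls after week 3, removes exactly the poorest week-3 responders in one arm and is random in the other, with an assumed change correlation of 0.7. Shift = φ(z)/(1 − p):

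- 10%: 0.1755/0.9 = 0.195 SD; 0.195 × 0.7 × 61.26 = 8.4 points (34% of 24.7).
- 20%: 0.2800/0.8 = 0.350 SD; 0.350 × 0.7 × 61.26 = 15.0 points (61%).

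**6. Gain from adjusting for baseline UFOV.** With equal visit variances and baseline correlation ρ (assumed), the adjusted contrast has (1 + ρ)/2 times the variance of the change-score contrast. With 98 per group:

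| ρ | Variance ratio | Effective d | Power |
|---|---|---|---|
| change score | 1 | 0.403 | 80% |
| 0.8 | 0.90 | 0.425 | 84% |
| 0.7 | 0.85 | 0.437 | 86% |
| 0.5 | 0.75 | 0.466 | 90% |

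This gain applies at week 3 as well as week 6.

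**The case against.** Much of the other side's case stands and limits the point.

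- A reader might infer that all these analyses use only participants with every visit. They do not: each change needs only baseline and its own visit, so someone lost after week 3 remains in the primary analysis. Only a classical mixed ANOVA needs all visits. That analysis is labelled exploratory, and its name does not rule out a likelihood fit, although the within-subject wording points to the classical form.
- Week 3 was chosen to limit loss. Someone lost before it leaves only a baseline value, so the benefit against dropout at the primary endpoint is close to nil.
- A reader might take "The main challenge will be the loss to follow-up" as a forecast of heavy loss between weeks 3 and 6. In the Discussion it follows the 1-, 3- and 6-month assessments and is answered there with reminders, caregiver involvement and remote assessment. It does not support that reading.
- A reader might infer a bias of 41% or 74% of the target by putting SD 74.8 into the extreme scenario (10.2 and 18.3 points). That pairs an SD with a target that together do not reproduce 98 per group, and it rests on deterministic loss in one arm.
- A reader might infer that a mixed model abolishes dropout bias. It does so only under missing at random and a correctly specified model.
- The article never says that only complete cases are used, and imputation or analysis sets may be defined in a plan not shown. That absence is no finding.

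What the objection does not remove is that the article fixes unadjusted change-score ANOVAs for both endpoints, and that this estimator, as named, makes no use of an observed week-3 value when week 6 is missing.

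**Conclusion.** The point holds in limited form. The stated method is valid if loss after week 3 is unrelated to outcome. If it depends on the week-3 response and differs by arm, the week-6 co-primary is biased by about 6–7% of the 24.7-point implied target at 10% dropout and 13–14% at 20%, with an extreme bound of about 8 and 15 points. These sizes rest on assumed correlations, dropout timing and dropout mechanisms; the documents give none of them. A likelihood-based model removes the bias under missing at random and only part of it otherwise. The separate gain from baseline adjustment does not depend on dropout and reaches the week-3 primary endpoint. This is a worthwhile improvement to a named method. It does not show that the week-3 primary analysis is invalid.

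**What to change.** Replace the separate change-score ANOVAs with one likelihood-based repeated-measures model:

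- Outcomes: UFOV at week 3 and week 6.
- Participants: all randomised with any observed post-baseline value, in their assigned arm.
- Terms: baseline UFOV, arm, visit, arm-by-visit and baseline-by-visit, with an unstructured covariance.
- Contrasts, pre-specified: the combined arm against each single-intervention arm, at week 3 and at week 6.
- State the missing-at-random assumption and add a sensitivity analysis for data missing not at random.

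This model can also take over the role of the exploratory mixed ANOVA for weeks 3 and 6. The cost is revised analysis wording, somewhat more pre-specification and one further sensitivity analysis. The model can be fitted in the software that the article names (SPSS 28). Sample size, visits and data collection do not change.

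### The primary test is an unadjusted change-score ANOVA, with covariates admitted only after a significant baseline difference; fixing baseline UFOV as a covariate would usually gain precision at no cost.

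*Protocol article*

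**What the plan says.** The Primary Outcomes section of the protocol article defines the endpoint as a change: "The primary outcome will be changes from baseline in the" UFOV at week 3, with week 6 as co-primary.

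Under Statistical Analysis, Primary Outcome, the test is stated in two steps: "This will be tested by calculating the delta (week 3 or 6—baseline"), and then "by performing independent one-way ANOVAS with intervention as a factor". Intervention is the only term in that model.

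The same paragraph gives the covariate rule. It refers to "several variables such as gender, depression or years of education" and continues: "if there are significant differences between groups after randomization, we will include those covariates in the analysis, performing ANCOVAS instead of ANOVAS". It names no significance level, and the list is given by example only. The section on MOCA, MMSE and GDS adds that the GDS is collected "to track depression levels that could be used as a covariate in the analysis", which leaves its use optional.

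Baseline UFOV is not put into the primary model as a covariate anywhere. The mixed-model ANOVA over time does use the baseline visit, as a level of the time factor, but it is labelled exploratory and does not replace the primary test.

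**The concern.** There are two separate issues.

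- **Use of baseline.** Subtracting baseline fixes its slope at 1. When the true slope of follow-up on baseline differs from 1, the subtraction leaves avoidable noise in the outcome. The article adds futility looks for feasibility and omits a fourth arm on grounds of cost, so precision that can be had without extra participants matters here.
- **Choice of covariates.** In a properly randomised trial, a significant baseline difference is a chance event. Testing for it says nothing about whether the variable predicts UFOV. A strong predictor that happens to be balanced stays out, and an irrelevant variable that happens to be imbalanced goes in. The form of the primary model is therefore unknown until the groups have been compared.

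This is a stated rule and not a detail left to a fuller plan. A later analysis plan could cure it only by reversing it.

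**Working it through.** **1. The plan's own figure.** The Sample Size section gives, for older adults, a mean (SD) difference "between UFOV applications was 56.2 (74.8") and, as cut-off, "the mean test-retest difference for younger adults, namely 31.5 (43.7"). The article does not show its formula, but this calculation reproduces its result:

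- Difference: 56.2 − 31.5 = 24.7
- SD: √((74.8² + 43.7²)/2) = √3752.4 = 61.26
- d = 24.7/61.26 = 0.403
- Two-sided two-sample t-test, alpha 0.05, power 0.80: n = 97.5, so 98 per group
- 10% attrition: 98/0.9 = 108.9, so 109 per group and 3 × 109 = 327 in total

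Pairwise power at 98 per group is 0.802. The SDs are those of test-retest differences, so the calculation matches an unadjusted change-score analysis.

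**2. Precision of change score and ANCOVA.** Let ρ be the baseline to follow-up correlation within arm and s² the variance, assumed equal at both visits.

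- Var(change) = 2(1 − ρ)s²
- Var(ANCOVA residual) = (1 − ρ²)s²
- Ratio = (1 + ρ)/2

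The documents give no ρ, so a range is shown. Power uses d/√ratio with d = 0.403.

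| Assumed ρ | Variance ratio | d/√ratio | Power at 98 per group | n per group for 0.80 |
|---|---|---|---|---|
| 0.4 | 0.70 | 0.482 | 0.919 | 69 |
| 0.6 | 0.80 | 0.451 | 0.881 | 79 |
| 0.8 | 0.90 | 0.425 | 0.841 | 88 |
| 0.9 | 0.95 | 0.414 | 0.822 | 93 |

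If the follow-up SD is k times the baseline SD, the two variances are (1 + k² − 2ρk)s² and k²(1 − ρ²)s². Their difference is (1 − ρk)²s², which is never negative and is zero only when the slope ρk equals 1. So the direction does not depend on equal variances, but the size does.

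**3. How often the rule switches the model.** With three independent covariates, each tested at 0.05 (level and independence assumed), the chance that at least one is significant under sound randomisation is 1 − 0.95³ = 0.143. With four it is 1 − 0.95⁴ = 0.185.

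**4. What the rule does to the test.** This was simulated with three arms of 98, normal scores and equal variances. Education and GDS each correlated 0.3 with baseline UFOV, and gender was unrelated to it. All three were tested at 0.05, and the significant ones were added to the change-score model. Under the alternative, one arm was better by 0.403 SD of change. Results are for the overall three-arm F-test (4,000 null and 3,000 alternative replicates).

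| ρ | Analysis | Type I error | Power |
|---|---|---|---|
| 0.5 | Change score, unadjusted | 4.7% | 83.6% |
| 0.5 | Article's conditional rule | 4.5% | 83.7% |
| 0.5 | ANCOVA with baseline UFOV | 4.4% | 93.2% |
| 0.7 | Change score, unadjusted | 5.4% | 82.9% |
| 0.7 | Article's conditional rule | 5.3% | 82.8% |
| 0.7 | ANCOVA with baseline UFOV | 4.9% | 89.2% |

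The rule was triggered in 13.9% to 14.6% of runs. The Monte Carlo standard error of a 5% rate is √(0.05 × 0.95/4000) = 0.34 points, so none of the type I figures differs materially from 5%.

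**The case against.** The change-score ANOVA is a legitimate analysis. It is unbiased under randomisation, fits the endpoint as defined, and matches the SDs behind the sample size. The trial also calls itself exploratory. All of that stands, and it makes this an improvement in efficiency and pre-specification, not the repair of an invalid test.

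The size of the gain is also uncertain. UFOV exposure is bounded (16.67 to 500 ms), so equal variances are doubtful, and at high correlations little is gained. That stands too.

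Three stronger readings are tempting, but the material does not support them:

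- A reader might infer that the conditional rule distorts the error rate of the primary test. The simulation shows no material inflation.
- A reader might infer that the trial already falls short of its stated power. The stated 98, 109 and 327 reproduce from the article's own inputs. Whether those inputs suit this population is a separate question.
- A reader might infer that gender, education and GDS must all be in the model. Nothing in the article shows that they predict UFOV; the gain computed here comes from baseline UFOV alone.

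Finally, because the covariate list is open, baseline UFOV could in principle be added. It would enter only through the same significance test, so this does not answer the point.

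**Conclusion.** The point holds as a matter of efficiency and of a badly fixed model choice. The primary analysis forgoes precision that an already measured baseline would usually supply. Relative to an always-adjusted ANCOVA, the power forgone at 98 per group is about 12 points at ρ = 0.4, 4 points at ρ = 0.8 and 2 points at ρ = 0.9. These figures assume equal variances and d = 0.403.

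The covariate rule makes the primary model depend on chance imbalance in roughly one trial in seven, given three independent covariates and a 0.05 level, neither of which the article fixes. In the setting simulated, it returned none of the forgone power. The change should be made, but the planned test would not be invalid without it.

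**What to change.** - State the primary analysis as an ANCOVA of the week-3 UFOV score on arm with baseline UFOV always included, and likewise for week 6.
- Delete the rule that admits covariates after a significant baseline difference. Baseline characteristics can be tabulated by arm without tests.
- If further covariates are wanted (for example GDS, education or gender), list them in advance on expected prognostic value and include them whatever the observed balance.
- Report change scores descriptively. The endpoint definition can stay: with baseline in the model, the estimated arm difference is the same whether the outcome is the follow-up score or the change.

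The cost is wording. Baseline UFOV is part of every participant's baseline assessment, and the GDS is already collected. Gender and years of education are named in the analysis section but not among the listed baseline measures, so their collection should be confirmed if they are to be used. The sample size need not change.
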